**Methods/Design:**

This is a prospective, monocentric, randomized, controlled clinical trial. A total of 80 adult patients suffering from a lumbar disc herniation (LDH; 40 treated surgically, 40 conservatively) are allocated in a ratio of 1:1. Patients in the treatment group will receive surface electromyography (EMG)-triggered electrical stimulation for eight weeks, whereas patients in the control group will not obtain any additional treatment. The primary outcome parameter is defined as the cold detection threshold (CDT), determined by quantitative sensory testing (QST), 24 months after intervention. Secondary outcome parameters include the inquiry of sensory nerve function by two-point discrimination and QST, the assessment of motor nerve function by manual muscle testing, and validated scales and scores. These include: the Oswestry Disability Index (ODI) and the Core Outcome Measures Index (COMI) assessing the domains pain, back-specific function, work disability, and patient satisfaction; the EQ-5D investigating the patient’s generic health status; the painDETECT questionnaire (PD-Q) to identify neuropathic pain components; and the Beck Depression Inventory (BDI) to assess severity of depression. Moreover, neurological status, pain medication usage, and blood samples (CRP, TNFα, IL-1β, IL-6) will be evaluated. Study data generation (study site) and data storage, processing, and statistical analysis are clearly separated.

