### Sample size calculation

Sample size calculation is based on the primary endpoint of the study, the cold detection threshold (CDT) two years post intervention. Relevant data were acquired from previous prospective trials at our center, also using the CDT as a primary outcome parameter. Sixty-three patients are required to detect a difference of 3.4 considering a standard deviation (SD) of 6.8 with 80% power on a two-sided level of significance of 0.05. We considered a loss to follow-up < 20% adequate for final calculation of sample size, which is 75–80 patients.

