### Statistical analyses

All statistical analyses will be performed in consultation with the Department of Medical Statistics and Health Economics, Innsbruck Medical University, Innsbruck, Austria. Detailed descriptive statistics will be provided for the data collected and 95% confidence intervals will be calculated for all relevant estimates. The primary analysis will follow as the randomized principle. All patients with a complete pre-treatment examination will be considered for inclusion into the population. Primary outcome parameter will be the CDT. We estimate that the 24 months change of the CDT in patients treated without SES will be approximately 10%, whereas patients treated with SES should show a better improvement up to 20% of the initial threshold. In a one-way analysis of variance (ANOVA) test, group sample sizes of 35 patients in each group achieve 80% power to detect a significant difference between the CDT estimates with an estimated standard deviation of 20%. To adjust for multiple pairwise comparisons, the critical *p* value for statistical significance was adjusted to *p* ≤ 0.05. Descriptive analyses will include reporting means (with SDs) for continuous variables and frequencies (with percentages) for discrete variables. One-way analysis of variance (or non-parametric Kruskal–Wallis equivalent) will be used to assess the difference in the primary outcome of CDT between those patients that received conventional therapy (without SES) and those who received SES. Differences between each patient, compared to the not affected body site, will be analyzed using paired t-test to adjust for the clustered nature of the thresholds for each patient.

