## Discussion

Sensory and motor nerve function improvement following LDH, especially the influence on time and the quality of recovery, are infrequently subjected to well-designed clinical trials. There is a need for data with validated modern outcome instruments to assess evidence-based prognosis for patients with sensomotoric dysfunction. The results of this study will detect the effect of EMG-triggered multichannel SES on the improvement of mechanical and thermal sensitivity and the effect on motor recovery and pain, associated with clinical and laboratory parameters. Furthermore, additional influencing factors on sensomotoric recovery may be identified and will hopefully lead allow treatment recommendations for patients with LDH accompanied by a sensomotoric deficit.

To guarantee a high scientific value, the outcome instruments used in this trial are adjusted to the latest standards in the literature among spinal and neurologic investigations. The QST is a valuable instrument for the objectification of sensory function [25, 34]. The MMT also depicts a highly valuable tool for the quantification of muscle power and therefore we utilize the possibility to avoid an investigator’s bias, not considered in most of the previous trials. Our patient’s self-assessment (ODI, EQ5D, COMI, PD-Q, BDI) matches the highest standards of the middle European assessments for quality of life and consequently subjective efficacy of spinal procedures and management options. Patients are treated in a standardized manner and are therefore well comparable. All quantitative values can be compared between the initial treatment groups (conservative or operative) as well as between the therapy groups (SES or non-SES) and, additionally, within each patient by collecting and comparing data bilaterally (affected and non-affected side). Furthermore, our SES program was developed with leading clinical specialists and therefore matches the latest standards and innovations. Devices are especially programmed so that after the scheduled application of the medical device, individual usage times and thresholds can be read and considered by the clinical investigators.

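### The critical p value said to be adjusted for multiple pairwise comparisons is the unadjusted 0.05, so the stated multiplicity control does not exist and its family of comparisons is undefined

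*Protocol article*

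**What the plan says.** Under Statistical analyses the protocol article gives a reason and a result in one sentence: "To adjust for multiple pairwise comparisons, the critical *p* value for statistical significance was adjusted to" p ≤ 0.05. Under Sample size calculation the trial is sized for one difference in CDT "with 80% power on a two-sided level of significance of 0.05".

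The primary question is narrow. The abstract fixes one endpoint at one time: "The primary outcome parameter is defined as the cold detection threshold (CDT), determined by quantitative sensory testing (QST), 24 months after intervention". The Statistical analyses section compares it by one-way ANOVA, or Kruskal–Wallis, "between those patients that received conventional therapy (without SES) and those who received SES". That is two groups and one contrast.

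Further comparisons appear elsewhere. The section on surface electrical stimulation sets out 1:1 allocation within each of two populations, surgical and conservative, which gives four cells of 20. The Discussion adds: "All quantitative values can be compared between the initial treatment groups (conservative or operative) as well as between the therapy groups (SES or non-SES", and also mentions comparing the affected with the unaffected side within each patient. No section says which of these are the multiple pairwise comparisons, how many there are, or how they are adjusted.

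**The concern.** The sentence asserts that multiplicity has been dealt with. It is therefore more than a detail left to an analysis plan, and the figure it gives contradicts it: the level after adjustment equals the level before.

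The primary test loses nothing by this. What is at stake is any further significance claim. The study objective names both populations, and the Discussion hopes to identify a superior management of disc herniation. Population-specific and between-population results are therefore likely to be reported. If the pooled SES comparison were negative and one population gave p = 0.04, the published rule would allow that result to be called significant after adjustment, although no adjustment had been made.

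**Working it through.** **Inputs.** The critical value is p ≤ 0.05 (Statistical analyses). The level used for sizing is 0.05 two-sided, with difference 3.4, SD 6.8 and 80% power (Sample size calculation). There are four cells of 20 (Surface electrical stimulation), or 16 each after a 20% loss. The number of comparisons k is not given and has to be assumed.

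**Step 1: is 0.05 the unadjusted level?** The plan's own sizing figure confirms it. With d = 3.4/6.8 = 0.5, the normal approximation gives 2 × (1.960 + 0.842)² / 0.5² = 62.8, so 63 per group, which is the article's number at two-sided 0.05 with no adjustment. (Whether the article means 63 per group or in total is a separate matter.) The same formula gives 84 per group at 0.05/3 = 0.0167 and 97 at 0.05/6 = 0.0083. No adjusted level entered the sizing.

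**Step 2: can 0.05 be an adjusted critical value?** The Bonferroni critical value is 0.05/k:

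| k | 0.05/k |
|---|---|
| 1 | 0.05 |
| 2 | 0.025 |
| 3 | 0.0167 |
| 4 | 0.0125 |
| 6 | 0.0083 |

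It equals 0.05 only for k = 1, when there is nothing to adjust. The primary analysis is that case, because a one-way ANOVA on two groups has a single contrast.

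**Step 3: what would testing each comparison at 0.05 cost?** All rows assume that no true differences exist.

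| Assumed family | Calculation | Family-wise error |
|---|---|---|
| Pooled SES versus none only | one test | 5% |
| SES versus none in each population | 1 − 0.95² | 9.75% |
| Those two plus the pooled test | simulation, equal strata, 400,000 runs: 0.1146 | about 11.5% |
| All six pairs of four cells, no gate | studentized range tail at 2.00 × √2 = 2.83, four groups, 60 df (16 per cell): 0.199; with 20 per cell: 0.200 | about 20% |

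**Step 4: how far does the last row depend on the missing gate?** If the six pairs were tested only after a significant four-group ANOVA, simulation with 20 per cell gives about 5% when all four cells are equal. It gives about 12% when three are equal and one differs greatly.

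**The case against.** The strongest reply is that the confirmatory claim is sound. There is one endpoint, one time point and one two-group contrast, for which 0.05 is the right level. This stands, and it is why the point is confined to additional claims.

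It also stands that no section plans the six cell-pair tests or a separate CDT test of SES within each population. The four cells come from the description of allocation, and the Discussion lists marginal and within-patient comparisons as possible, not as confirmatory. Four of the six cell pairs cross the two populations, and initial therapy is not randomized. A reader might infer that the trial, or its primary analysis, runs a 20% false-positive risk. The article does not support that reading: the figure needs all six pairs, no overall test first, and no true difference anywhere.

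A charitable reading is that adjusted p values will be compared with 0.05. The text says instead that the critical value was changed, and it names neither a procedure nor a family, so the sentence would need rewriting even then.

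Finally, a full multiplicity scheme belongs in an analysis plan, which is not shown, and its absence from a condensed article is no fault. That is accepted. The fault is the positive statement that an adjustment was made.

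**Conclusion.** The sentence is wrong as written. For any number of comparisons above one, a critical value of 0.05 is no adjustment, and the family it is meant to cover is not defined. The primary SES contrast on CDT at 24 months is unaffected.

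For further pairwise claims, the error depends on a family that the article does not state. Under no true differences and 0.05 per test it runs from 9.75% (two populations) through about 11.5% (pooled test added) to a conditional worst case of about 20% (six cell pairs without a gate). The severity is moderate: a false assurance about secondary claims, with no change to the primary test or its sizing.

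**What to change.** Delete the sentence. State that SES versus no SES in all randomized patients, on CDT at 24 months, is the only confirmatory test, at two-sided 0.05 with no adjustment.

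Then choose one of two courses for everything else:

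- Report population-specific and other pairwise comparisons as supportive estimates with 95% confidence intervals, without significance claims. This is the simpler course and fits the intervals that the article already promises.
- If some of them are to carry significance claims, list them and name a procedure, for example Holm for the two population-specific SES contrasts once the pooled test is significant, or Tukey for cell pairs.

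The change takes one or two sentences and should be made before any outcome data are analysed. It costs the primary test no power. The price is that significance is harder to claim for secondary pairwise comparisons.

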### Study population

The study protocol aims to include patients who suffer from a LDH with radiculopathy and a sensomotoric nerve dysfunction. Patients are naturally divided into two groups, whether their individual condition qualifies them for lumbar sequestrectomy according to the guidelines of DGNC and DGOOC (Population 1) or for initial conservative treatment (Population 2). If conservative treatment (including usage of pain medication according to the WHO level scheme and physiotherapy for all, and epidural steroid injection in exceptional cases, like therapy refractory radicular pain without motor deficit) is inefficient for more than six weeks, or if patients suffer from a severe paresis, surgical treatment will be performed. Population 2 is thus allowed to cross over to Population 1. Surgically treated patients will receive postoperative pain therapy according to the WHO level scheme but no additional active physiotherapy in the first eight weeks after surgery, except SES. Radiculopathy is defined as pain, paresis (muscle strength grade 4 or less), or a sensory dysfunction in a specific nerve root distribution area L3 to S1. Additionally, a radiologically determined pathology at treatment level investigated by MRI needs to correlate to the clinical symptoms. To minimize risk factors for an unfavorable outcome, patients with significant co-morbidities (see inclusion and exclusion criteria in, Additional file 2: Table S2) need to be excluded, as this may mask a difference in treatment efficacy. Informed consent is obtained from each participant.

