### Surface electrical stimulation

After a guideline-dependent decision of the initial treatment for LDH, patients will be randomized into two groups, respectively, in a 1:1 allocation ratio: 20 patients (50%) in Population 1 and 20 patients (50%) in Population 2 will receive SES, whereas the other half will follow standardized treatment algorithms adjusted to the initially chosen therapy for LDH (see Additional file 3: Figure S1).

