### Randomization

The allocation ratio within groups is 1:1 (see Additional file 3: Figure S1). The randomization code will be generated independently from the clinical investigators according to a random permuted blocks method with varying block size. Statistical Software Stata 10.0 module Ralloc version 3.5.2 (Statacorp College Station, TX, USA) will be used to generate the random code. An independent statistician will administer the randomization code.

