## Abbreviations

ANCOVA: Analysis of covariance
DGNC: German Society of Neurosurgery
DGOOC: German Society of Orthopaedics and Orthopaedic Surgery
EMG: Electromyography
MRC: Medical Research Council
MRI: Magnetic resonance imaging
WHO: World Health Organization

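### The primary one-way ANOVA of CDT omits the population within which patients are randomized and the baseline CDT; the comparison stays unbiased but is inefficient and can be conservative

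*Protocol article*

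**What the plan says.** The section *Statistical analyses* of the protocol article names the primary test: "One-way analysis of variance (or non-parametric Kruskal–Wallis equivalent) will be used to assess the difference in the primary outcome of CDT". The two groups are defined by SES alone, so this is a two-group comparison pooled over both populations. The power statement in the same section also rests on a one-way ANOVA.

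The design is stratified. Once the initial treatment has been decided, "patients will be randomized into two groups, respectively, in a 1:1 allocation ratio", and "20 patients (50%) in Population 1 and 20 patients (50%) in Population 2 will receive SES" (*Surface electrical stimulation*). The section *Randomization* agrees: "The allocation ratio within groups is 1:1".

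The two populations receive different background care. Conservative patients all have physiotherapy, whereas surgical patients have "no additional active physiotherapy in the first eight weeks after surgery, except SES" (*Study population*).

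A complete pre-treatment examination is the condition for entering the analysis population, and the expected effect is expressed as a percentage of the initial threshold. Baseline CDT is therefore available.

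The outcome scale is described in two ways. *Sample size calculation* gives the endpoint as "the cold detection threshold (CDT) two years post intervention". *Statistical analyses* plans on a 24-month change of 10% without SES against up to 20% with SES, with an SD of 20%.

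**The concern.** A one-way ANOVA has a single factor. Randomizing within population balances the arms on population, so a CDT difference between populations does not add to the real variability of the SES estimate. Without a population term, however, that difference stays in the residual variance. The standard error is then too large, the confidence interval too wide and the test conservative.

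Baseline CDT is likely to predict 24-month CDT, and the named test does not use it as a covariate. Efficiency that could be had without any new data is given up. This matters here because, on the article's own effect and SD, the trial has well under 80% power.

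**Working it through.** **Inputs from the article.** Difference 3.4 and SD 6.8, so d = 3.4/6.8 = 0.5; two-sided alpha 0.05; 80% power; loss to follow-up below 20%; 75–80 patients. The second statement, 10 percentage points with SD 20%, also gives d = 0.5. With 80 patients and 20% loss, 64 are evaluable, or 32 per arm.

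**Assumptions, not given in the article.** The correlation rho of baseline with 24-month CDT, shown at 0.3, 0.5 and 0.7. The share R² of CDT variance explained by population, shown at 5, 10 and 20%; with equal strata, 20% corresponds to populations 1 within-population SD apart, since 0.25/(1 + 0.25) = 0.20.

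**1. The plan's own figure.** n per arm = 2(1.96 + 0.84)²/0.5² ≈ 63 (64 with the t distribution). So 63 is a per-arm number; the article uses it as a total, since 63/0.8 ≈ 79 falls in its 75–80. Power of the unadjusted test (t-based) is 50% at 32 per arm, 54% at 35 and 60% at 40. The 80% claimed at 35 per group is not reproduced. That is a separate error, and it sets the starting point here.

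**2. Effect of leaving out population.** With total SD 6.8 and balanced allocation within population, the true standard error is √(1 − R²) times the one the ANOVA estimates. The true critical value is therefore 1.96/√(1 − R²). With the term included, the effective d is 0.5/√(1 − R²). At 32 per arm:

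| R² | true critical z | true alpha, no term | power, no term (normal approx.) | power, with term (normal approx.) |
|---|---|---|---|---|
| 0 | 1.96 | 0.050 | 52% | 52% |
| 5% | 2.01 | 0.044 | 52% | 54% |
| 10% | 2.07 | 0.039 | 52% | 56% |
| 20% | 2.19 | 0.028 | 52% | 61% |

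The population term is worth about 2 to 9 points.

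**3. Effect of leaving out baseline, two readings of the SD.**
- If the SD is that of the 24-month value, the ANCOVA residual SD is SD·√(1 − rho²), so d becomes 0.5/√(1 − rho²).
- If the SD is that of the change from baseline (equal variances at both times), the ANCOVA residual SD is SD·√((1 + rho)/2), so d becomes 0.5/√((1 + rho)/2).

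Power at 32 per arm, t-based, without the population term:

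| rho | d, 24-month SD | power | d, change SD | power |
|---|---|---|---|---|
| 0.3 | 0.524 | 54% | 0.620 | 69% |
| 0.5 | 0.577 | 62% | 0.577 | 62% |
| 0.7 | 0.700 | 79% | 0.542 | 57% |

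The comparator is 50% in each case: the one-way ANOVA of the 24-month value under the first reading, and of the change under the second. ANCOVA gains throughout, but the pattern over rho reverses between the readings.

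**4. What adjustment cannot do.** Under the 24-month-SD reading, 80% power at 32 per arm needs rho = √(1 − 32/63) ≈ 0.70; at 35 per arm it needs √(1 − 35/63) ≈ 0.67. At rho 0.5 the total needed is still 96 evaluable patients.

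**The case against.** **Baseline may already be used.** Because the planning paragraph speaks of change relative to the initial threshold, the ANOVA could be of change. This stands as an ambiguity, and it rules out saying flatly that baseline plays no part. It does not remove the point: a one-way ANOVA of change still has no population term, and ANCOVA gains under that reading too, although only from 50% to 57% at rho 0.7.

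**The unadjusted test is valid.** This is correct. A reader might infer bias or an inflated type I error; the documents support neither, because allocation is balanced within population and the error rate is at or below 5%.

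**The populations may hardly differ.** The *Background* reports substantial improvement over 24 months under both treatments, and nothing in the article gives a CDT difference between populations. One could calculate that power falls to about 41% by adding a 1 SD population difference on top of SD 6.8. The article does not say that 6.8 is a within-population SD. If it is the total SD, unadjusted power stays near 50%.

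**The Kruskal–Wallis alternative and the abbreviation list.** A reader might see the missing switching rule as an invitation to pick a test after seeing the data. Such a rule is commonly left to an analysis plan, and none is shown here, so it is not counted as a defect. The entry "ANCOVA: Analysis of covariance" in *Abbreviations*, unused in the article, might be taken as a sign of a dropped method; it is no evidence of anything, because the supplementary material is not shown.

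**Conclusion.** The point holds as a loss of efficiency, not as a threat to validity. The article explicitly names a primary test that does not reflect its own within-population randomization and does not adjust for a baseline it requires, and it leaves the outcome scale unsettled.

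Baseline adjustment gains about 4 to 29 points of power at 32 per arm if the planning SD is that of the 24-month value, and about 7 to 19 points if it is that of the change, over assumed rho 0.3 to 0.7. The gain from the population term and the degree of conservatism depend on R², which is also assumed. The direction is secure; the size is not. In particular, 79% power should not be read as what ANCOVA would deliver, since it needs both rho 0.7 and one of the two readings of the SD.

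**What to change.** State one primary analysis: ANCOVA of 24-month CDT with terms for randomized arm, population as randomized (not as later treated, since conservative patients may cross over to surgery) and baseline CDT, reporting the adjusted mean difference with its 95% confidence interval. With baseline CDT in the model, the arm effect is the same whether the outcome is the 24-month value or the absolute change, so this also settles the outcome scale. State which quantity the planning SD refers to. Keep a rank test stratified by population as a sensitivity analysis only.

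The change is one of wording. It needs no new data and costs two degrees of freedom. It does not replace correcting the sample-size section, where a per-arm requirement of 63 is used as a total; that must be dealt with separately.

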The patient’s sensory and motor recovery after a LDH, whether treated surgically or not, is influenced by various factors like gender, pain, duration, and severity of paresis [14, 22, 34]. Further parameters include: the degree of nerve root compression; functional recovery of nerve fibers; and potentially denervated muscle areas [27]. Electromyography (EMG)-triggered surface electrical stimulation (SES) is an intervention combining electrical biofeedback of muscles with neuromuscular electrical stimulation. It is known to be effective in improving weakness of paretic muscles and remodeling the function of the related nervous system [40]. SES is frequently used to further improve motor function in severe central and peripheral paresis, as muscle atrophy due to damage on the innervating nerve is prevented by active and passive stimulation of the muscle, as well as stimulation of the according nerve [2, 9, 19, 23, 30]. Previous studies not only showed a positive influence of electrical stimulation on promotion of peripheral nerve regeneration after injury in humans and animals [11, 15, 39], but also showed an increase in strength and muscle size in healthy subjects [20]. Additionally, patients with painful IVDD show elevated IL-6 and TNF-α levels not only in the IVDD itself [7, 17], but also in serum [36]. Electrical stimulation may lead to a downregulation of these pro-inflammatory cytokines [8, 33]. Nevertheless, the underlying mechanism of SES and its influence on sensomotoric recovery are still unclear and require further investigation.

So far, improvement of sensory and motor nerve function supported by SES has been infrequently subjected to well-designed clinical trials. Thus, there is a need for data with validated modern spinal outcome instruments (i.e. quantitative sensory testing [QST], objectively assessed muscle force, and patient’s self-assessment regarding satisfaction and ability). The objective of this prospective clinical trial is thus to evaluate the efficacy of EMG-triggered SES on sensomotoric recovery in patients with LDH, treated either conservatively or surgically, using validated modern spinal outcome instruments.

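### The affected-versus-unaffected side data go only into a within-patient paired t-test, so they add nothing to the SES-versus-control comparison, which itself stands

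*Protocol article*

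**What the plan says.** The Background section sets a between-arm objective: to "evaluate the efficacy of EMG-triggered SES on sensomotoric recovery in patients with LDH". The Statistical analyses section then describes two separate analyses.

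- **SES versus no SES.** A one-way ANOVA, or Kruskal-Wallis in its place, "will be used to assess the difference in the primary outcome of CDT between those patients that received conventional therapy (without SES"), the other group being the SES arm. The unaffected side does not appear in this sentence.
- **Affected versus unaffected side.** The sentence reads: "Differences between each patient, compared to the not affected body site, will be analyzed using paired t-test to adjust for the clustered nature"; the clustering meant is that of thresholds within a patient.

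The Discussion keeps the two apart. After naming the comparisons between initial treatments and between SES and non-SES groups, it adds a further comparison, "additionally, within each patient by collecting and comparing data bilaterally (affected and non-affected side"). Nowhere does the article compare the side difference between randomized arms or enter the unaffected side as a covariate.

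**The concern.** A paired t-test of affected against unaffected side asks whether the mean side difference is zero. The trial asks whether SES changes recovery. Under Surface electrical stimulation, the electrodes are placed in the distribution area of the affected root, so a natural question is whether the side deficit is smaller with SES. The planned test cannot answer it. Pairing deals with the two thresholds being measured in the same patient, but only for the side contrast; it adds nothing to the treatment comparison.

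Two things are at stake. The unaffected side may explain part of the between-patient variation in CDT, and the arm comparison as stated does not use it. Also, the article does not say what the paired result is for, so it could be read as bearing on SES when it does not.

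**Working it through.** **Inputs.** Sample size calculation: "Sixty-three patients are required to detect a difference of 3.4 considering a standard deviation (SD) of 6.8 with 80% power", two-sided 0.05, so d = 3.4/6.8 = 0.5. Statistical analyses: "group sample sizes of 35 patients in each group achieve 80% power to detect a significant difference between the CDT estimates", with 10% against 20% change and SD 20%, again d = 0.5. Final size: "We considered a loss to follow-up < 20% adequate for final calculation of sample size, which is 75–80 patients". With 80 randomized and 20% lost, 64 remain, or 32 per arm. The correlation ρ is not in the article, so a range is used.

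**The plan's own figure.** Normal approximation: n per arm = 2 × (1.960 + 0.842)² × (6.8/3.4)² = 2 × 7.85 × 4 = 62.8, so 63 per arm and 126 in total. The article uses 63 as a total. That is a separate matter, but it is why the baseline power below is near 52% and not 80%.

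**What the paired test responds to.** Simulation of 4,000 trials per case, 32 per arm, SD 6.8 on each side, assumed ρ = 0.6:

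| Case | Paired test, arms pooled, rejects | Between-arm test of side difference rejects |
|---|---|---|
| No SES effect, residual deficit 3.4 | 99% | 5% |
| No SES effect, residual deficit 2 | 73% | 5% |
| SES effect 3.4, deficit 3.4 without SES | 57% | 58% |

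The first row can be checked by hand. SD of the side difference = 6.8 × √(2 × 0.4) = 6.08; SE with 64 patients = 6.08/8 = 0.76; 3.4/0.76 = 4.47; power = Φ(4.47 − 1.96) = 99%. The pooled paired test follows the size of the deficit. It rejects most often where SES does nothing and the deficit is large. The between-arm test holds its 5% level.

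**What the unaffected side could add to the arm comparison.** Power ≈ Φ(3.4/SE − 1.96), with SE = SD × √(2/32) = SD/4.

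- Affected side alone: SE = 1.70, 3.4/1.70 = 2.00, power = Φ(0.04) = 52%.
- Unaffected side as covariate: SD = 6.8 × √(1 − ρ²).
- Raw side difference as outcome: SD = 6.8 × √(2(1 − ρ)), assuming equal SDs on both sides and no SES effect on the unaffected side.

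| ρ (assumed) | Covariate: SD | Power | n per arm for 80% | Side difference: SD | Power | n per arm for 80% |
|---|---|---|---|---|---|---|
| 0.3 | 6.49 | 55% | 58 | 8.05 | 39% | 88 |
| 0.5 | 5.89 | 64% | 48 | 6.80 | 52% | 63 |
| 0.7 | 4.86 | 80% | 33 | 5.27 | 73% | 38 |

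The covariate gains at any ρ other than zero. The raw difference gains only above ρ = 0.5 and loses below it.

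**Limit of the table.** For the covariate, ρ is the correlation between 24-month affected-side CDT and the unaffected-side value entered. The columns treat it as the only covariate. If baseline affected-side CDT is also in the model, it may take up part of the same variation, and the unaffected side's own share will be smaller. The article gives nothing from which to split the two.

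**The case against.** The strongest reply is that the paired test is faulted for not answering a question it was never given. The SES question belongs to the ANOVA in the preceding sentence, the bilateral comparison is described as additional, and a paired test is a proper method for it. All of that stands. So does the point that covariates and sensitivity analyses are often left to an analysis plan, which is not shown here. The abbreviation list even includes ANCOVA, although no analysis in the text uses it. What remains is that the article does specify a test for the side data, and that test is disconnected from the randomized comparison.

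Two stronger readings are tempting and not supported.

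- A reader might infer that the trial has no valid SES comparison. It has one, through the ANOVA on CDT.
- A reader might infer that the paired test will be run in each arm and a significant result in one arm set against a non-significant one in the other. With no SES effect, exactly one of two independent tests of power p is significant with probability 2p(1 − p): 50% at p = 0.5, and 32% at p = 0.8 or 0.2. Those are error rates of a procedure that the article does not describe. It does not say whether the test is pooled or run by arm, nor that p-values will be contrasted. This is a risk of misreading, not a planned rule.

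It is also fair to say that the gain may be small: at ρ = 0.3, only from 52% to 55%.

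**Conclusion.** The point holds as a missed opportunity and an unclear label, not as a flaw in the primary comparison. The paired t-test is sound for residual side deficit and silent on SES, and the stated arm comparison leaves the unaffected side out. With the unaffected side as covariate, power would be about 55% to 80% for assumed correlations of 0.3 to 0.7, against 52% without it. This rests on d = 0.5, 32 per arm, a normal approximation, and the unaffected side as the only covariate. The true correlation is unknown from the article, so the range shows what is possible and does not predict the result. Comparing raw side differences is not a safe replacement for the primary variable, since it would lower power at correlations below 0.5.

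**What to change.** Amend the Statistical analyses section in three places.

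1. Compare 24-month affected-side CDT between randomized arms by ANCOVA, with population at randomization, baseline affected-side CDT and baseline unaffected-side CDT as covariates. Take the unaffected-side value from before randomization, so that treatment cannot have influenced it.
2. Name one secondary or sensitivity analysis: the 24-month affected-minus-unaffected difference compared between arms, adjusted for the baseline side difference. Do not make it the primary variable.
3. Keep the paired t-test, state whether it is pooled or by arm, and label it a description of residual deficit and not evidence on SES.

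The cost is wording and two simple models. The Discussion says data are collected on both sides, so no new measurement should be needed, provided that QST is bilateral at baseline and at 24 months. The visit plan is a figure that is not shown, so this should be confirmed. If the center's earlier CDT studies, used for the sample size, measured both sides, the sponsor could estimate the correlation from them and replace the assumed range.
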